### How Missing Data Will Be Handled in the Analysis

We will handle missing data points resulting from dropouts or noncompliance using multiple imputation methods. To fully appreciate the potential influence of missing responses, sensitivity analyses will be done to examine whether the imputation method affects outcomes and whether missing data are missing-at-random.

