### Criteria for Discontinuing or Modifying Allocated Intervention and Comparator

If a participant decides to discontinue the exercise intervention, they will be asked to return for a follow-up visit to complete the week 26 assessments. The reason for discontinuation will be documented. Participants are free to withdraw from participation in the study at any time upon request. An investigator may discontinue a participant from the study, including but not limited to the following reasons: lost to follow-up, unable to contact participant, any event, medical condition, or situation occurs such that continued collection of follow-up study data would not be in the best interest of the participant, or the participant meets an exclusion criterion (either newly developed or not previously recognized) that precludes exercise. In this scenario, the participant would still be followed for outcomes.

If a participant is unable to complete a specific exercise due to injury or discomfort, but still wants to complete the intervention, the Neuro Exercise Specialists will adapt the exercises for that participant while still targeting the intended muscle group as best as possible.

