#### Primary Outcomes

The primary outcomes for the study are feasibility, adherence, and safety of the combined exercise intervention. Adherence and feasibility will only be evaluated in the exercise group. Feasibility will be measured using the average percentage of HRmax for endurance exercise sessions and the average repetition maximum for resistance exercise sessions. Adherence will be measured using the average number of days exercised per week, the duration of exercise for resistance exercise, and the duration of exercise at target HR intensity for endurance exercise. Participants will keep track of exercise sessions using exercise diaries, which investigators will use to assess adherence. Data from Polar HR monitors will be used to assess feasibility. Safety will be measured by the incidence of adverse events (AEs) and serious AEs in the exercise and control groups.

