#### Statistical Methods for Primary and Secondary Outcomes

The primary outcomes are feasibility, adherence, and safety of the combined exercise program. To assess feasibility, we will estimate the overall average %HRmax for endurance training and average repetition maximum for resistance training and their corresponding 95% CIs for the exercise group at 26 weeks. We will then compare the average to the intended target intensity (82.5% for endurance exercise and 10-RM for resistance training) using a 1-sample *t* test (*α*=.05). We will use repeated measures ANOVA of weekly %HRmax and linear mixed models to assess any trends over time from weeks 7 to 26, including a random effect for time within participant as sample size permits. To measure adherence in the exercise group, the average number of days per week exercised and the duration of time (minutes) exercised at the specified intensity will be calculated. Achievement of the adherence (hypothesized to be at least 3 d/wk) will be tested using 1-sided, 1-sample Student independent group *t* tests. To assess safety, the incidence of individual AEs (including serious AEs) and exact CIs will be calculated. We will use Fisher exact or Poisson exact tests to compare exercise and control groups for AEs that are definitely, probably, or possibly related to the exercise intervention as categorical variables.

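### The imputation rule for noncompliance does not exempt the primary adherence outcome, so it permits weeks without exercise to be filled in as exercised weeks

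*Protocol article*

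**What the plan says.** All references are to the protocol article.

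- **How Missing Data Will Be Handled in the Analysis** gives one general rule: "We will handle missing data points resulting from dropouts or noncompliance using multiple imputation methods". It adds that "sensitivity analyses will be done to examine whether the imputation method affects outcomes and whether missing data are missing-at-random". No outcome is named or exempted.
- **Primary Outcomes** restricts the relevant population: "Adherence and feasibility will only be evaluated in the exercise group". It defines the measure: "Adherence will be measured using the average number of days exercised per week", together with duration of resistance exercise and duration at target heart rate for endurance exercise. It names the source: "Participants will keep track of exercise sessions using exercise diaries, which investigators will use to assess adherence". Table 1 sets the window at weeks 7-26.
- **Statistical Methods for Primary and Secondary Outcomes** says that "the average number of days per week exercised and the duration of time (minutes) exercised at the specified intensity will be calculated". The test is then given: "Achievement of the adherence (hypothesized to be at least 3 d/wk) will be tested using 1-sided, 1-sample Student independent group" *t* tests.
- **Criteria for Discontinuing or Modifying Allocated Intervention and Comparator** says of people who stop exercising that "they will be asked to return for a follow-up visit to complete the week 26 assessments".
- **Strategies to Improve Adherence to Intervention and Comparator** provides for a weekly call that covers, among other things, how many days the participant exercised.

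**The concern.** The rule lists noncompliance beside dropout as a source of missing data to be imputed. That can be reasonable for a week-26 MoCA or a biomarker. For adherence it is not, because noncompliance is what the outcome measures. A week in which someone assigned to exercise did none contributes zero days and zero minutes. Imputing that week from exercised weeks, the person's own or others', replaces the failure with an estimate of success.

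The request that people who stop should return at week 26 adds to the ambiguity. A person who stops exercising but attends has real week-26 data. A person who does not attend is largely covered by the word dropout already. Among the records that noncompliance most directly leaves blank are diary entries and heart-rate uploads, which are the source data for adherence and feasibility.

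At stake is a headline primary result. The distortion grows with the amount of non-exercise, so it would be largest where adherence is poorest. The planned sensitivity analyses would not reveal it: they vary the imputation method and question missing at random, but nothing in them scores a missed session as zero.

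**Working it through.** **Is there a plan figure to reproduce?** No. The article gives no expected adherence, SD or power for the adherence test. Its sample size rests on other outcomes (14 per group with 12% attrition: 28 / 0.88 = 31.8, stated as 31), and nothing below depends on it.

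**Inputs from the article.** 16 participants planned for the exercise group (Sample Size); a 20-week window, weeks 7-26, so 16 × 20 = 320 person-weeks; target 3 d/wk, one-sided, one-sample test.

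**Assumed inputs.** Mean days per week while active (c), numbers stopping and when, between-participant SD 0.6, and one-sided alpha 0.05 (the article states 0.05 for the feasibility test but no alpha for this one).

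**Step 1: size of the overstatement.** With f the fraction of person-weeks not exercised:

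- mean with zeros = c × (1 − f)
- mean after imputation from active weeks ≈ c
- overstatement ≈ c × f

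At c = 3.8:

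| Assumed stopping | f | Mean with zeros | Imputed mean | Overstatement |
|---|---|---|---|---|
| 3 of 16 after week 12 | 3 × 14 / 320 = 0.131 | 3.30 | 3.80 | 0.50 |
| 4 of 16 after week 10 | 4 × 16 / 320 = 0.20 | 3.04 | 3.80 | 0.76 |
| 5 of 16 after week 10 | 5 × 16 / 320 = 0.25 | 2.85 | 3.80 | 0.95 |

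**Step 2: when is the target truly missed?** The true mean falls below 3 when f > 1 − 3/c, which at c = 3.8 is f > 0.21. Only the third row qualifies. The first two show an overstated mean, not a false claim that the target was met.

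**Step 3: effect on the test.** After imputation at the active level, t = (3.80 − 3) / (0.6 / √16) = 0.80 / 0.15 = 5.3, so the test passes almost always. Simulation of 20,000 trials per scenario agrees. The pass rate with zeros is 2.6%, 0% and 0% in the three rows, and about 100% with imputation in all three.

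**Step 4: check with actual multiple imputation.** 2,000 trials per scenario, 20 imputations, within-participant missing-at-random imputation, Rubin's variance, within-participant SD 0.8, weeks capped at 5 days (so means sit slightly below the nominal c):

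| Active rate c | Assumed stopping | Mean, zeros | Pass, zeros | Mean, imputed | Pass, imputed |
|---|---|---|---|---|---|
| 3.5 | none | 3.48 | 91% | 3.48 | 91% |
| 3.5 | 2 of 16 halfway | 3.26 | 24% | 3.47 | 91% |
| 3.5 | 4 of 16 halfway | 3.05 | 0.2% | 3.48 | 90% |
| 3.5 | 4 of 16 after 5 of 20 weeks | 2.82 | 0% | 3.47 | 88% |
| 4.0 | 5 of 16 after 4 of 20 weeks | 2.95 | 0% | 3.91 | 100% |

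With no stopping the two methods agree. The last two rows are false passes.

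**Step 5: a milder case.** Suppose stopping ran at the planned 12% attrition, about 2 of 16 (0.12 × 16 = 1.9), and both did nothing throughout the window. Then f = 40 / 320 = 0.125, and a true mean below 3 needs c < 3 / 0.875 = 3.43. At c = 3.8 the true mean is 3.8 × 0.875 = 3.33, still above target.

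**The case against.** A reader might infer that the plan will fill in exercise that was never done and so inflate adherence. The article does not support that. It imputes missing data points and never says that an unexercised week is one, or that days per week will be imputed; the methods section says only that the average will be calculated. The weekly calls should turn many unexercised weeks into recorded zeros while the participant stays in contact. This objection stands, and it is why the bias is permitted rather than certain.

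Nor does noncompliance have to mean missed exercise. It could be a declined lumbar puncture, a missed visit window, an unkept diary or a heart-rate file not uploaded. Imputing values that are truly unknown is ordinary practice. This also stands, but the rule as worded covers both kinds without separating them.

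The compliance figures above are all assumed. The only withdrawals reported (Recruitment and Retention) are two controls, who do not enter the adherence outcome. Withdrawal is not the same as ceasing to exercise, but nothing shown supports any particular stopping rate.

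Scoring conventions are often left to an analysis plan, and their absence from an article would not be a finding. Here, however, the article states a rule, and as stated it reaches a primary outcome for which it is unsuitable.

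A reader might also infer that the authors believe the data can prove missing at random. They call the work a sensitivity analysis, and a delta-adjusted analysis fits that label. What remains is that observed data cannot decide the question, so the wording should say what will be done.

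**Conclusion.** The point holds in limited form. The stated rule covers all data missing through dropout or noncompliance and does not exempt adherence, where not exercising is the outcome. If it were applied to weeks after stopping or to blank diary weeks, mean days per week would be overstated by about c × f, and the 3 d/wk criterion could be met with a true mean below 3. In the assumed illustration with 5 of 16 stopping after week 10, that is 2.85 against about 3.80. With fewer or later stoppers the mean is still overstated, but the true mean may remain above target, so no false claim follows. The actual size is unknown, because the article gives no compliance data and does not say how unexercised weeks are coded. The planned sensitivity analyses do not close the gap.

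**What to change.** Before analysis begins (planned for June 2026), amend the missing-data section to state:

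1. For adherence, weeks 7-26 count for every participant randomised to exercise. Known non-exercise, including after stopping, is scored as 0 days and 0 minutes.
2. Multiple imputation is limited to confirmed recording or upload failures and to week-26 outcomes that were not obtained.
3. The sensitivity analysis for missing at random is a delta-adjusted (tipping-point) analysis of the week-26 outcomes.

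This is a change of wording only. Diaries and weekly calls should already supply the information needed to score the zeros. The one downside is that the reported adherence figure may be lower. If zeros were always intended, the result does not change.

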### Sample Size

We based the sample size calculations on the secondary outcomes of efficacy. Since adherence and feasibility can only be evaluated in the exercise group and are not collected in the control group, it is not possible to calculate power comparing these outcomes between groups. The power and sample size analysis is based on the biomarker of interest, klotho, and the global cognition measure, MoCA. Based on prior studies describing changes in klotho plasma levels with exercise in healthy sedentary adults [33,34], a sample size of 14 participants per group is expected to detect an effect size of 100  pg/mL, considering a type I error of 0.05 with a statistical power of 0.85. Assuming a maximum attrition rate of 12%, we decided to recruit a total of 31 participants (16 participants in the exercise group and 15 in the control group). With respect to cognition, prior endurance exercise and resistance training studies show benefits on cognition at 6 or 12 months [17,35], but Chang et al [36] have shown that endurance exercise for 8 weeks leads to a statistically significant improvement in MoCA (1.6-point increase). Based on our sample size of 31, we will have 80% power with a 2-sided type I error of 0.05 to detect a significant improvement in MoCA.

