### Plans to Promote Participant Retention and Complete Follow-Up

A maximum attrition rate of 12% was accounted for in our sample size analysis. We currently have 2 participants left to randomize and have lost 2 to follow-up. Throughout the study, we have implemented multiple strategies to increase participant retention and minimize loss to follow-up. This includes (1) planning the intervention at home with virtual supervision for exercise sessions so participants do not need to frequently travel to the clinic; (2) the study team will offer additional phone calls, supervised sessions, or in-person assistance at the research center for any participants in need of support throughout the intervention; (3) video tutorials will be provided to participants, so they feel comfortable using the equipment and completing the exercises; and (4) trainers will be available to make any exercise modifications as necessary so participants can continue to complete the intervention.

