### Recruitment and Retention

As with many clinical trials, recruitment can be a challenge for multiple reasons. A 26-week-long intervention poses a significant burden on participants, especially as this includes assessment visits in the clinic and 2 lumbar punctures to collect CSF. However, thus far, there has been ample interest in our study through the Movement Disorders clinic at UCSF, and we foresee no issues with completing recruitment. Our attrition rate thus far has been low, with only 2 control group participants electing to withdraw from the study and not returning for the final visit. Additionally, we are alleviating participant burden to the best of our abilities by using an at-home intervention and providing all necessary equipment. Our aim is that this, combined with frequent phone check-ins and trainer-supervised sessions, will keep adherence high.

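### One stated aim of the missing-data sensitivity analyses, to examine whether data are missing at random, cannot be met from observed data; robustness to stated departures should replace it

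*Protocol article*

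**What the plan says.** The section *How Missing Data Will Be Handled in the Analysis* has two sentences. The first fixes the main approach: "We will handle missing data points resulting from dropouts or noncompliance using multiple imputation methods". The second gives the purpose of the sensitivity analyses, "To fully appreciate the potential influence of missing responses", and then their two aims: "sensitivity analyses will be done to examine whether the imputation method affects outcomes and whether missing data are missing-at-random". The section names no imputation model and no scenario in which data are missing not at random.

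On the losses themselves, *Plans to Promote Participant Retention and Complete Follow-Up* states: "We currently have 2 participants left to randomize and have lost 2 to follow-up". *Recruitment and Retention* places both losses in one arm: "only 2 control group participants electing to withdraw from the study and not returning for the final visit". *Sample Size* allows for up to 12% attrition and plans "16 participants in the exercise group and 15 in the control group". *Blinding* says that participants know their group. *Strengths and Limitations of the Study* acknowledges that clinical assessments are made only before and after the intervention period.

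**The concern.** Data are MAR when, given what was observed, the chance that a value is missing does not depend on the value itself. The missing week-26 scores are the evidence needed to judge this, and they are not there. One mechanism that is MAR and another that is not can yield the same observed data set. An analysis plan that follows this wording would take on an aim that it cannot fulfil. This is an aim that the article states, not a detail that it leaves to another document.

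Comparing imputation methods does not settle the matter by itself. If every method compared assumes MAR, their agreement says nothing about departures from it.

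Two features of this trial make the assumption carry weight. The reported withdrawals were voluntary and came from an unblinded waitlist arm. And no intermediate MoCA, motor or biomarker measurement is scheduled, so the imputed week-26 value of a dropout rests on baseline data and the assumption. What is at stake is the week-26 group comparison of the secondary and exploratory outcomes.

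**Working it through.** **Inputs from the protocol article**
- Planned arms: 16 exercise, 15 control (*Sample Size*).
- Losses so far: 2 control, none reported in exercise (*Recruitment and Retention*). The count is interim, with 2 participants still to be randomized when it was written.
- Cited MoCA change: 1.6 points, from a study of endurance exercise (*Sample Size*).
- Power claim for MoCA: 80% at two-sided 0.05 with 31 participants. No SD is given.

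**The plan's own figure.** 14 per group is 28 in total. 28 / (1 − 0.12) = 31.8, which rounds up to 32. The stated 31 is one fewer, which is close enough not to matter here.

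**Size of the loss on planned denominators.** 2/15 = 13.3% of controls against 0/16 in exercise, and 2/31 = 6.5% overall. Fisher's exact test gives p = 0.23, so the split is compatible with chance. The actual denominators may differ, because simple randomization does not guarantee 16 and 15.

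**Shift from a departure from MAR.** Suppose that the true week-26 values of both missing controls differ from their MAR-imputed values by δ points. The control mean, and so the group difference, moves by (2/15) × δ. The documents give no δ, so the range is an assumption.

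| δ (MoCA points) | Shift in group difference | Share of 1.6 |
|---|---|---|
| 1 | 0.13 | 8% |
| 2 | 0.27 | 17% |
| 3 | 0.40 | 25% |

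If the MAR-based difference were 1.6, δ from −3 to +3 would give true differences from 2.0 down to 1.2. The observed data are the same throughout that range, so they cannot tell these cases apart.

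**Effect on a test.** This step needs an SD. Assume that the 80% power refers to a between-group difference of 1.6 points with 16 and 15 participants. The t-based SD of change is then 1.54. The article does not say that 1.6 is that difference, so this is an assumption. SE = 1.536 × √(1/16 + 1/15) = 0.552, with 29 degrees of freedom. Shifts of 0.13, 0.27 and 0.40 move the t statistic by 0.24, 0.48 and 0.72.
- *Clear result.* A difference of 1.6 gives t = 2.90, p = 0.007. An adverse δ of 2 gives (1.6 − 0.267)/0.552 = 2.42, p = 0.022. An adverse δ of 3 gives 1.2/0.552 = 2.17, p = 0.038. The conclusion stands. If the SE uses the 13 observed controls (27 degrees of freedom), these become p = 0.028 and 0.046.
- *Borderline result.* A result at p = 0.04 has t = 2.15. An adverse δ of 2 gives 2.15 − 0.48 = 1.67, p = 0.11. A favourable δ of 2 gives 2.63, p = 0.013.

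**Could a check on observed data help?** Comparing baseline values of those missing and those observed addresses only whether data are missing completely at random. Its power to detect a 1 SD difference at two-sided 0.05 is about 23% (2 against 13 controls) or 26% (2 against 29 participants). A null result would say almost nothing.

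**The case against.** The strongest reply is that the sentence already has a robustness purpose and a robustness check. It opens by asking how much missing responses matter, and its first aim is whether the imputation method changes the outcome. It does not restrict the methods to those that assume MAR. The second aim may be loose shorthand for sensitivity to the MAR assumption, and the choice of methods and ranges is what a condensed article commonly leaves to an analysis plan. This stands in part: the first aim is sound and should be kept, and the absence of a named method is no fault. It does not rescue the second aim, which as worded asks a question that the data cannot answer.

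A reader might infer that the plan tests MAR instead of robustness, or that it will produce false reassurance. The documents support neither. The first aim is a robustness check, and nowhere does the article say that a finding about MAR will be used to validate the main analysis.

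A reader might also take 2 of 15 against 0 of 16 as reported differential dropout. It combines an interim count with planned arm sizes, and the difference is compatible with chance. No reasons for withdrawal are given, so that these two participants departed from MAR is a possibility, not a finding.

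Finally, the borderline example starts at the edge of significance, where small shifts in either direction matter. A departure of 2 points is 1.3 of the assumed SD (2/1.536), in both dropouts and in the same direction. These points limit the size of the problem, and the conclusion is scaled to them.

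**Conclusion.** The concern holds in a limited form. The stated aim of examining whether data are missing at random cannot be met, and the check on imputation method probes departures from MAR only if a method that allows them is included, which the text does not state.

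The effect is modest. With 2 of a planned 15 controls missing and assumed departures of 1 to 3 MoCA points, the group difference shifts by 0.13 to 0.40 points. That could overturn a borderline result. On the assumed SD of 1.54, a 1.6-point difference would remain significant across that range. The result rests on three assumptions: the range of δ, the planned arm sizes as denominators, and, for the p-values only, the reading of 1.6 points as the between-group difference behind the power claim. Further losses before the end of follow-up would change the figures.

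The primary outcomes are not touched in this way. Feasibility and adherence are assessed in the exercise group only, and safety is an incidence of events, not an imputed week-26 score.

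**What to change.** Keep the check on whether the imputation method affects outcomes. Delete the aim of examining whether data are missing at random, and state that MAR is an assumption that the observed data cannot test.

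Add a delta-adjusted (tipping-point) analysis. Impute under MAR, then shift the imputed week-26 values of participants with missing data over a prespecified range that is varied separately by arm. Report the shift at which the conclusion changes. Do this for MoCA (for example 0 to ±3 points), MDS-UPDRS part III and the biomarkers, each with a range on its own scale. Fix the ranges before the between-group results are examined; analysis is scheduled to start in June 2026.

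The cost is a sentence or two of wording and a few extra analysis runs on data already being collected. The conclusion may turn out less firm, which would be the honest result if it depends on two unseen values.
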